### Data analysis

The sensitivity and specificity values for the photographic caries assessment will be estimated and compared to the reference visual dental assessment at the baseline. Kappa statistic will be used to estimate the inter-rater reliability of the photographic dental assessments by two independent OHTs. 15% of dental images will be re-examined to test intra-rater reliability at least, 4 weeks after the initial review of images.

The baseline data will be used to generate descriptive statistics for the intervention and control groups (teledental versus usual care pathway). General linear regression models will be performed to compare the efficacy of the interventions on decay (mean DFT/dft) between intervention and control groups, adjusting for baseline data collected via a survey that includes tooth brushing (yes/no; frequency); dental visit patterns over the past year, child age, Indigenous status, Socio-Economic Indexes for Areas (SEIFA), private insurance status and educational level of parents. The measure of intervention efficacy will be the difference between the intervention and control groups in adjusted DFT/dft (caries incidence) per child. All analyses will be performed using SAS (version 9.4). In addition, a cost minimisation analysis will be undertaken to compare the costs associated with teledental versus the usual pathway of dental care over 9 months. This will include both the cost of the initial screening, and any subsequent interventions occurring over the 9 months. The analysis will be conducted from the perspective of the health system and, will not take into consideration the costs incurred by the families. All salaries used in the calculation will be based on Australian government rates and will include on-costs.

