**Methods/design:**

We describe an ongoing parallel, two-armed, non-inferiority randomised controlled trial that compares routine and teledental pathway of dental care in children aged 4–15 years (*n* = 250). Participating schools in Western Australia will be randomly assigned to the control or teledental group, approximately three schools in each group with a maximum of 45 children in each school. All participants will first receive a standard dental examination to identify those who require urgent referrals and then their teeth will be photographed using a smartphone camera. At the baseline, children in the control group will receive screening results and advice on the pathway of dental care based on the visual dental screening while children in the teledental group will receive screening results based on the assessment of dental images. At 9 months follow-up, all participants will undergo a final visual dental screening. The primary outcomes include decay experience and proportion of children become caries active. The secondary outcomes include the diagnostic performance of photographic dental assessment and costs comparison of two pathways of dental care.

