### Allocation

To avoid spill-over effects within a school, we will conduct randomisation using the school as the unit of allocation because the intervention is implemented at the level of the school (Fig. 3). The schools will be randomly allocated in a 1:1 ratio to one of the teledental or control group. For allocation of the participants, a computer-generated list of random numbers will be used. To approximate equality of sample sizes in the study groups, we will use block randomisation with computer-generated randomly permuted blocks of 4 at each school. School-specific randomisation lists are concealed by an independent researcher, and kept in sequence and opened as participants are examined at the baseline and found eligible for enrolment. The research team and data analysts will be blinded to group allocation and will not be aware of the randomisation procedure. Study participants (and their parents/guardians) and OHTs providing the intervention and/or collecting data cannot be blinded to group allocation.

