### Sample size calculation

The sample size calculation is based on a two-sided 95% CI for a single proportion using the Z-test approximation, an effect size of 0.1 and an expected observed proportion of 0.90. The number of participants with caries that meet the power of 0.8 is estimated to be 35 [n ≥ (Z^2^/m^2^) p (1 - p)]. With the prevalence of caries at 35% (1.86 × 65), 65 participants without caries are needed. After considering a 20% drop out rate, the proportion that gives the largest sample size shows that at least 125 children per group will be needed. Three schools will be required in each group with a maximum of 45 children in each school.

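### The article makes the school the unit of allocation, about three per arm, but the only efficacy model it names is a per-child regression with no school term, so run as written its standard errors omit between-school variance

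*Protocol article*

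**What the plan says.** On allocation, the Allocation section says "we will conduct randomisation using the school as the unit of allocation because the intervention is implemented at the level of the school", giving the avoidance of spill-over as the reason, and adds "The schools will be randomly allocated in a 1:1 ratio to one of the teledental or control group". The abstract has "approximately three schools in each group with a maximum of 45 children in each school" and the Sample size calculation section repeats "Three schools will be required in each group with a maximum of 45 children in each school".

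The same Allocation section also describes "block randomisation with computer-generated randomly permuted blocks of 4 at each school", with a separate list for each school that is opened as children are enrolled.

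On analysis, the Data analysis section names one efficacy model: "General linear regression models will be performed to compare the efficacy of the interventions on decay (mean DFT/dft) between intervention and control groups". The covariates are tooth brushing, dental visits over the past year, and "child age, Indigenous status, Socio-Economic Indexes for Areas (SEIFA), private insurance status and educational level of parents". The effect measure is "the difference between the intervention and control groups in adjusted DFT/dft (caries incidence) per child". School is not among the covariates. No random effect, generalised estimating equation, cluster-robust standard error or school-level comparison is named. The sample size section contains no ICC and no design effect.

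**The concern.** When schools are randomised, the arm difference carries the variation between schools as well as the variation between children. A general linear regression on children, in its ordinary meaning, assumes independent errors. It estimates the standard error from child-to-child variation on roughly 200 degrees of freedom, whereas the comparison rests on six schools and 6 − 2 = 4 degrees of freedom.

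The article gives reason to expect that schools differ. Study setting draws them from different parts of Western Australia. Background describes a social gradient in oral disease and services concentrated in metropolitan areas. A chance difference between two sets of three schools could then be read as an effect of the pathway, or could hide one. In a trial described as non-inferiority, an interval that is too short can also support a claim of equal effectiveness that the data do not justify.

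**Working it through.** **The plan's own figure.** With Z = 1.96, p = 0.90 and m = 0.1 (Sample size calculation):
- n = Z² p(1 − p)/m² = 3.84 × 0.09/0.01 = 34.6, so 35 children with caries.
- At 35% prevalence, 35 × 0.65/0.35 = 65 without caries, total 100.
- 100/(1 − 0.20) = 125 per group.
- 125/45 = 2.8, so three schools per group.

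Every step reproduces, and none allows for clustering.

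**Inputs for the check.** Three schools per arm; 100/3 = 33.3 completers per school, or 125/3 = 41.7 enrolled. The ICC is not in the article; 0.005 to 0.10 is assumed.

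**Formulas.**
- Design effect: DE = 1 + (m − 1) × ICC, where m is now children per school.
- Ratio of correct to naive standard error: √DE.
- True two-sided error of a nominal 5% test: 2[1 − Φ(1.96/√DE)].
- Width of a valid school-level 95% interval relative to the naive one: √DE × 2.78/1.96, where 2.78 is the t quantile on 4 degrees of freedom.

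Example at m = 33.3 and ICC 0.05: DE = 1 + 32.3 × 0.05 = 2.62; √DE = 1.62; 1.96/1.62 = 1.21; two-sided error 22.6%; width ratio 1.62 × 2.78/1.96 = 2.29.

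| ICC (assumed) | DE, m = 33.3 | √DE | Two-sided error | Width ratio | Two-sided error, m = 41.7 | Width ratio, m = 41.7 |
|---|---|---|---|---|---|---|
| 0.005 | 1.16 | 1.08 | 6.9% | 1.53 | 7.4% | 1.55 |
| 0.01 | 1.32 | 1.15 | 8.8% | 1.63 | 9.8% | 1.68 |
| 0.02 | 1.65 | 1.28 | 12.7% | 1.82 | 14.6% | 1.91 |
| 0.05 | 2.62 | 1.62 | 22.6% | 2.29 | 26.0% | 2.47 |
| 0.10 | 4.23 | 2.06 | 34.1% | 2.91 | 38.4% | 3.19 |

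**Simulation check.** 40,000 trials per setting, three against three schools of 33 children, normal outcome, no true difference, no covariates. The test that ignores school rejected in 5.1%, 9.1%, 12.7%, 22.7% and 34.5% of trials at ICC 0, 0.01, 0.02, 0.05 and 0.10. A t-test on the six school means stayed at 4.9% to 5.1%.

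**The case against.** Five points can be made for the plan.

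1. *Children may be randomised within schools.* The blocks of four and the school-specific lists read that way, and under such a design leaving school out would not inflate the error in this manner. This stands as a condition. The weight of the text favours school-level allocation: the abstract, two explicit sentences with a rationale in Allocation, and the Visual dental examination section, which refers to the group allocation of the school. The conflicting sentence still has to be resolved.

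2. *The article condenses a fuller plan.* No sentence says that children are treated as independent; that is inferred. Variance structure and degrees of freedom are often left to an analysis plan. But the article goes further than silence: it fixes the model, its covariates and a per-child effect measure, and its sample size has no design effect. The stated model does not match the stated allocation.

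3. *The illustration is unadjusted.* The covariates may explain part of the variation between schools, so the residual ICC may sit at the low end of the range. That is fair. They do not stand in for a school term and do not restore school-level degrees of freedom.

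4. *SEIFA.* A reader might infer that this area index is largely confounded with six schools. The article does not support that. It lists SEIFA with the baseline survey data, so it may be coded by each child's home area and vary within a school.

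5. *Non-inferiority error.* A reader might infer a specific rate of false non-inferiority claims. The article gives no margin and no decision rule for the efficacy interval; its 95% interval belongs to the single-proportion sample size. No such rate can be derived.

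**Conclusion.** The point holds, conditional on schools being the randomised unit. The efficacy model as stated would then give standard errors that are too small whenever the residual ICC is positive. The direction does not depend on the size of the ICC, but the amount does. With about 33 completers per school, the two-sided error is about 7% at ICC 0.005 and 34% at 0.10, against a nominal 5%. These are unadjusted illustrations on assumed ICCs, not predictions for this trial. The co-primary proportion of children becoming caries-active faces the same problem if it is analysed child by child.

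**What to change.** First reconcile the Allocation section: state whether schools or children within schools are randomised, and amend the sentence on blocks and school-specific lists to agree.

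If schools are randomised, replace the efficacy model with one of the following:
- **Two-stage.** Regress DFT/dft on the child-level covariates without the arm term, average the residuals by school, and compare the six school means by t-test on 4 degrees of freedom (number of schools minus two if it is not six).
- **Mixed model.** Add a random school intercept and use Kenward-Roger degrees of freedom, which the planned SAS software can fit. With so few schools, a mixed model or robust standard error without a small-sample correction would also be unreliable.

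Apply the same principle to the caries-active proportion, and report the ICC for both outcomes.

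The change needs no further enrolment, and the article reports data collection as still under way, so it can be specified before analysis. The cost is precision. Over ICC 0.01 to 0.10 the valid interval is roughly 1.6 times (33.3 per school) to 3.2 times (41.7 per school) as wide as the naive one, and the sample size was never set for the efficacy comparison. Six schools may leave that comparison imprecise, and the plan should say so and word its conclusion accordingly.

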### Outcome assessment

*Primary outcomes* include decay experience in either dentition as measured by the DFT/dft (decay, filled teeth) index at the baseline and 9-month follow up. Teeth will be classified as carious if have arrested caries, caries into dentine or enamel level caries. In addition to the proportion of children becomes caries-active at the 9-month follow-up which refers to the percentage of children developing one or more new caries in any of the previously caries-free teeth when assessed at the baseline. Data will be collected from one of our system’s functional components running on the backend to automatically record dental assessments based on dental images and through the oral health assessment forms completed by OHTs in the control group.

*Secondary outcomes* include the diagnostic performance of photographic dental assessment versus standard dental examination at the baseline. The participants’ dental care utilisation patterns collected via a baseline survey (Additional file 2) and adapted from Kopycka-Kedzierawski et al. [36]. Also, costs comparison between the two pathways of dental care will be conducted to identify the least costly alternative. The resources for the usual pathway of dental care will include vehicle costs, admin costs (e.g. telephone appointments, printing services and postage) and costs of consumables used in visual dental screening and the dental practitioner’s time. The resources for the teledental pathway of dental care include: software licence fees, ICT equipment, Internet and software engineer’s time, admin costs (e.g. telephone appointments, printing services and postage), costs of consumables used in dental photography, tele-assistants (photographer) time, and offsite dental practitioners’ time for reviewing dental images. Dental care costs for all children include the following: restorations, restorations with crowns and extractions. The costing data will be based on those incurred by the health system and will be derived from a survey and web-based open-access sources [37].

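### The DFT/dft efficacy model adjusts for survey items only, omits each child's baseline DFT/dft, and leaves open whether the outcome is the 9-month value or the change

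*Protocol article*

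**What the plan says.** The Outcome assessment section of the protocol article gives the first primary outcome as "decay experience in either dentition as measured by the DFT/dft (decay, filled teeth) index at the baseline and 9-month follow up". The Abstract and the section on the visual dental examination show that all participants have a standard visual examination at baseline, so the count is available for every child.

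The Data analysis section then sets the comparison: "General linear regression models will be performed to compare the efficacy of the interventions on decay (mean DFT/dft) between intervention and control groups". Its account of the covariates opens with "adjusting for baseline data collected via a survey that includes tooth brushing (yes/no; frequency); dental visit patterns over the past year, child age". Four social and family items complete the list, namely "Indigenous status, Socio-Economic Indexes for Areas (SEIFA), private insurance status and educational level of parents". The measure of efficacy is the "difference between the intervention and control groups in adjusted DFT/dft (caries incidence) per child". The section's other stated use of baseline data in comparing the groups is descriptive: "The baseline data will be used to generate descriptive statistics for the intervention and control groups".

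On design, the Allocation section says "we will conduct randomisation using the school as the unit of allocation", and the Sample size calculation section asks for three schools in each group.

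**The concern.** The article names an adjustment set and says where it comes from: a survey. Baseline DFT/dft comes from the clinical examination, so it falls outside that set. It is the same index on the same child nine months earlier, and can be expected to predict the outcome better than brushing or insurance status.

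The outcome is written as mean DFT/dft but the effect is called incidence. A 9-month count adjusted only for survey items is mainly a measure of prevalence, because it includes decay and fillings present before the pathways diverged. A change from baseline would be closer to incidence, but no sentence says that a change is analysed.

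Two things are at stake. One is precision. The other is exposure to chance differences in baseline decay, which are likely when only about six schools are randomised. In a non-inferiority trial such a difference can mask or mimic inferiority.

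**Working it through.** **The plan's own figure.** (1.96/0.1)² × 0.90 × 0.10 = 34.57, rounded up to 35 with caries. 35 × 0.65/0.35 = 65 without caries. The total is 100, and 100/(1 − 0.20) = 125 per group. The stated 125 reproduces. It is a precision calculation for a proportion and contains no DFT/dft variance, so nothing below changes it.

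**Inputs.** From the document: three schools per group and 100 completers per group, hence about 33 per school. Assumed, because the document gives neither: r, the correlation of baseline with 9-month DFT/dft after the planned survey covariates (0.5 to 0.9), and the intraclass correlation (ICC, 0 to 0.10). Standard deviations are taken as equal at both times, and results are in SD units.

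**Precision.** Relative to the 9-month value without baseline, the residual variance is 1 − r² with baseline as a covariate and 2(1 − r) for a change score. The ratio of the two is (1 + r)/2.

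| r | Variance left vs 9-month value | Variance left vs change score | Detectable difference with baseline added (SD) |
|---|---|---|---|
| 0.5 | 75% | 75% | 0.34 |
| 0.7 | 51% | 85% | 0.28 |
| 0.8 | 36% | 90% | 0.24 |
| 0.9 | 19% | 95% | 0.17 |

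The last column is (1.96 + 0.84) × √(2(1 − r²)/100), against 0.40 SD for the 9-month value without baseline. It treats children as independent and is therefore a best case.

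**Chance baseline gap, three schools against three.** SD of the gap = √(2[1 + (m − 1)ICC]/(3m)), with m = 33.3:

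- ICC 0: 0.14 SD; probability of a gap above 0.2 SD, 16%
- ICC 0.02: 0.18 SD; 27%
- ICC 0.05: 0.23 SD; 38%
- ICC 0.10: 0.29 SD; 49%

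**How much of a gap reaches the estimate.** For the 9-month value, a share r. For a change score, a share 1 − r with the sign reversed. At ICC 0.05 (gap SD 0.229) and r = 0.7 these are 0.7 × 0.229 = 0.16 SD and 0.3 × 0.229 = 0.07 SD. At r = 0.5 both are 0.11 SD.

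**Simulation check.** Six schools of 33 children, no true effect. SD of the estimated difference for 9-month value / change / baseline as covariate:

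- ICC 0.05, r 0.5: 0.169 / 0.171 / 0.126
- ICC 0.05, r 0.7: 0.192 / 0.123 / 0.103
- ICC 0.05, r 0.9: 0.215 / 0.066 / 0.062
- ICC 0.10, r 0.7: 0.225 / 0.134 / 0.100

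The covariate model was the most precise in every scenario tried. The simulation lets schools differ at follow-up only through baseline, which favours that model. Real schools would keep some further variation that baseline does not remove.

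**The case against.** The strongest reply is that incidence, for an index measured at two times, naturally means an increment. Baseline would then already be in the outcome, and at r of 0.7 to 0.9 the covariate saves only 5% to 15% of the variance. This stands as a possible reading, and it rules out asserting a large loss of precision outright. It does not settle the matter, because the modelled outcome is written as mean DFT/dft and no increment is defined.

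Second, the index has no missing component and the children are 4 to 15 years old, so shed or extracted teeth leave the count. The planned survey covariates also absorb some shared variance. Both points can lower the relevant r, which is why 0.5 is included. A lower r weakens the case against the 9-month value but strengthens the case for a covariate over a change score.

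Third, this is a condensed article and the analysis plan is not shown. The sentence does not exclude further covariates. It does, however, name an adjustment set and its source, and the outcome's own baseline lies outside both.

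A reader might infer more than the documents support:

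- That a baseline gap passes in full into the effect. Only a share r does, and only if the 9-month value is analysed. Chance imbalance after randomisation is a matter of precision, not bias.
- That the gap could match the decay expected over nine months. The document gives no expected increment or SD.
- That the caries-active outcome has the same defect. No regression is stated for it, and its definition already refers to teeth that were caries-free at baseline.

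The Allocation section also mentions permuted blocks of 4 at each school, which does not fit school-level allocation. The imbalance argument rests on the school-level reading. The precision argument holds on either.

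**Conclusion.** The point holds in a limited form. The stated covariates are survey items, baseline DFT/dft is not among them, and the text does not say whether the level or the change is analysed. The gain from adding baseline runs from large (19% to 51% of the residual variance left, for the 9-month value at r of 0.7 to 0.9) to modest (85% to 95% left, for a change score at the same r). At r = 0.5 it is 75% on either reading. The direction is the same throughout; the size depends on an assumed partial r and on an outcome definition that the article leaves open. The conclusion that most of the precision is certainly being lost is not supported. This should be corrected, but it does not invalidate the comparison.

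**What to change.** State in the Data analysis section whether the outcome is 9-month DFT/dft or its change from baseline, and add baseline DFT/dft as a covariate alongside age and the survey items. With baseline in a linear model, both outcomes give the same estimated group difference, so the ambiguity no longer affects the result.

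Name the visual examination as the source of the baseline value in both arms. This needs saying because the Outcome assessment section describes image-based records from the system and visual forms for the control group, and a covariate measured by different methods in the two arms would not adjust evenly.

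The cost is one model term. The data are already collected, and the Study status section says collection was still under way, so the term can be fixed before analysis. The change does not replace accounting for school clustering.

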#### Objectives

To determine the efficacy of a novel teledental pathway of dental care in improving oral health outcomes of school children relative to the usual pathway of dental care. *Hypothesis: The teledental pathway of dental care would be as effective as a routine pathway of dental care in improving children’s oral health.*To compare the costs of the teledental and usual pathway of dental care in school children, from a health system perspective. *Hypothesis: The teledental pathway of dental care would be cost-saving relative to the usual pathway of dental care.*To assess the diagnostic performance of dental screening on the basis of dental images relative to the reference visual dental inspection at the baseline. *Hypothesis: The photographic dental assessment will be as accurate and reliable as the standard visual dental screening.*

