## Methods

This community-based project is a parallel, two-armed, non-inferiority randomised controlled trial (RCT) that seeks to determine the efficacy and net economic benefits of using telehealth to facilitate dental care delivery within school settings and aid in generating data which will assist to leverage the planning and justification for a multicentre large RCT. The study will be conducted in accordance with the SPIRIT Statement for reporting a clinical trial protocol [33] (checklist provided as Additional file 1).

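### The trial is labelled non-inferiority, but no margin is stated for either primary outcome, and the printed sample size was not derived from one

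*Protocol article*

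**What the plan says.** The Abstract and the opening of Methods both give the design as non-inferiority; Methods has "two-armed, non-inferiority randomised controlled trial (RCT) that seeks to determine the efficacy and net economic benefits". The first hypothesis under Objectives is "The teledental pathway of dental care would be as effective as a routine pathway of dental care".

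Outcome assessment names two primary outcomes: DFT/dft, and the proportion of children who become caries-active by 9 months. Diagnostic performance and costs are secondary.

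Under Sample size calculation, "The sample size calculation is based on a two-sided 95% CI for a single proportion using the Z-test approximation", with "an effect size of 0.1 and an expected observed proportion of 0.90". A power of 0.8 is mentioned.

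Under Data analysis, a general linear regression compares mean DFT/dft between groups, and "The measure of intervention efficacy will be the difference between the intervention and control groups in adjusted DFT/dft (caries incidence) per child". No analysis is named for the caries-active proportion. The section then adds that "a cost minimisation analysis will be undertaken to compare the costs associated with teledental versus the usual pathway of dental care over 9 months". Outcome assessment says that the purpose of the cost comparison is to find the cheaper pathway.

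**The concern.** A non-inferiority claim means that the new pathway is not worse than the old one by more than a stated amount. Without that amount, no result can establish or refute the claim. The article gives no such amount in the hypotheses, the outcomes, the sample size or the analysis.

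Two things are at stake. First, the main conclusion has no criterion. The hypothesis is one of equal effectiveness and the analysis yields a plain difference, so a reader could be left to take an inconclusive difference as support. Second, a cost-minimisation analysis compares costs alone and so presupposes comparable outcomes. It is planned with no printed condition on the efficacy result, and without a margin nothing in the plan can establish that premise.

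**Working it through.** **1. Reproducing the stated sample size.** Inputs from Sample size calculation: Z = 1.96, m = 0.1, p = 0.90, caries prevalence 35%, dropout 20%.

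- n = (Z²/m²) × p(1 − p) = (1.96²/0.1²) × 0.90 × 0.10 = 34.6, so 35 with caries.
- 35/0.35 = 100 children, that is 35 with and 65 without caries.
- 100/(1 − 0.20) = 125 per group.

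The calculation closes exactly. It contains no margin and no between-arm comparison. The 0.1 acts as the half-width of an interval around one proportion, and children are split by caries status, as one would do for sensitivity and specificity. The stated power is not used: with a power term, (1.96 + 0.84)² × 0.09/0.01 ≈ 71, not 35.

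**2. Could 0.1 serve as the margin?** Assume that it is an absolute margin on the caries-active proportion, with no true difference, one-sided 2.5%, 80% power and no clustering. Then n per arm = (1.96 + 0.84)² × 2p(1 − p)/0.1². The article gives no control rate, so p is assumed.

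| Assumed control rate | Evaluable per arm | After 20% dropout |
|---|---|---|
| 10% | 142 | 178 |
| 20% | 252 | 315 |
| 35% | 358 | 448 |

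The plan expects 125 × 0.8 = 100 evaluable per arm.

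**3. What margin could 100 per arm support for mean DFT/dft?** No SD or intraclass correlation (ICC) is given, so the result is in SD units over assumed ICCs. With three schools per arm, about 33.3 evaluable children per school, the design effect is 1 + (33.3 − 1) × ICC. The margin giving 80% power is (1.96 + 0.84) × √(2/n_eff).

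| Assumed ICC | n_eff per arm | Margin, SD units |
|---|---|---|
| 0 | 100 | 0.40 |
| 0.02 | 60.7 | 0.51 |
| 0.05 | 38.2 | 0.64 |

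These use normal quantiles, so they do not yet allow for there being only six schools.

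**4. How informative is non-significance?** Assume 30% caries-active in the control arm, 45% in the teledental arm, and 100 completers per arm.

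- Individual-level test, no clustering: SE = √[(0.30 × 0.70 + 0.45 × 0.55)/100] = 0.0676, and 0.15/0.0676 = 2.22. The chance of a non-significant two-sided 5% result is about 40%.
- School-level t-test on 4 df (six schools, two arms), non-central t, with n_eff of about 75.6, 60.7 and 38.2 at ICC 0.01, 0.02 and 0.05: about 68%, 73% and 81%.

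The individual-level test is the nearer match to the regression printed under Data analysis. The school-level test respects the unit of allocation, but the article does not describe it.

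**The case against.** The strongest reply has four parts.

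- **The estimand is proper.** A non-inferiority trial does estimate a between-arm difference, and a general linear model supplies the confidence limit to set against a margin. This stands: the regression does not contradict the design. The comparison rule could also sit in an analysis plan that is not shown. The margin is harder to excuse, because it is an input to sizing and the article prints a complete sizing derivation without it. A margin added later would not have sized the trial.
- **No decision rule is printed.** A reader might infer that a non-significant difference will be reported as equal effectiveness. The article does not say so; it gives no significance rule at all. This is a risk left open by the missing criterion, not a stated plan.
- **The 68–81% figures come from a test that is not planned.** This also stands. Under an individual-level test without clustering the figure is about 40%, so a 15-point harm would more often be detected than missed. Both sets rest on assumed rates for the caries-active outcome, not on mean DFT/dft.
- **Costs do not ignore worse health altogether.** A reader might infer that they do. But the costed items include restorations, crowns and extractions over the 9 months, so decay that is treated enters the costs. Only untreated decay escapes, and DFT/dft is reported as a primary outcome in any case.

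Methods also says that the trial is meant to help plan a larger multicentre trial. That makes an estimation framing reasonable, but it does not supply a margin.

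**Conclusion.** The point holds, and its core needs no assumption: the design claims non-inferiority, no margin is given for either primary outcome, and the 125 per group follows exactly from single-proportion precision suited to a secondary objective. As written, the plan cannot deliver a non-inferiority conclusion.

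The size of the problem depends on assumed control rates, SDs and ICCs. Treating 0.1 as the margin does not rescue the sample size: at the control rates tried, the 100 expected per arm falls short by a factor of about 1.4 to 3.6 (142/100 to 358/100), before clustering. The non-significance figures are illustrations only.

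The cost-minimisation point is real but subordinate: no condition on efficacy is printed, and untreated decay is not captured in the costs.

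**What to change.** The Study status section says that data are still being collected, so the change can be made before analysis.

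1. State and justify a margin for each primary outcome: a difference in mean DFT/dft, and percentage points for the caries-active proportion. Claim non-inferiority only if the upper limit of the school-adjusted 95% confidence interval for teledental minus control lies below it.
2. If no defensible margin is achievable at this size, drop the non-inferiority label, report estimates with intervals, and state that the sample size rests on diagnostic precision.
3. Make the cost-minimisation conclusion conditional on non-inferiority being shown. Otherwise report the differences in cost and in DFT/dft together, with intervals.

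The cost is a change of wording in the protocol and analysis plan. The drawback is that the conclusions may have to be weaker than the non-inferiority label suggests.
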